## Abstract

**Background:**

The Goldilocks Work Principle expresses that productive work should be designed to promote workers’ health. We recently showed that it is feasible to develop and implement modifications to productive work that change physical behaviors (i.e. sitting, standing and being active) in a direction that may promote health among industrial workers. Therefore, the aim of the present study is to conduct a cluster randomised controlled trial investigating health effects of implementing the Goldilocks Work intervention among industrial workers.

**Methods:**

Our implementation plan consists of educating work teams, organizing implementation meetings, and providing feedback to workers. Three meetings with a preselected local workplace group will be scheduled. The first meeting educates the group to use a planning tool by which work can be planned to have ‘just right’ physical behaviors. The second and third meetings will focus on supporting implementation of the tool in daily work. An expected 28 clusters of work teams across two participating production sites will be randomized to either intervention or control group. Data collection will consist of 1) questionnaires regarding work and musculoskeletal health, 2) wearable sensor measurements of the physical behavior, and 3) assessment of general health indicators, including BMI, blood pressure, and fat percentage. The primary outcome is musculoskeletal health, measured by low back pain intensity, and secondary outcomes are 1) physical behaviors at work, 2) accumulated time in long bouts of sitting, standing, and being active and 3) perceived fatigue and energy during work. Furthermore, implementation and cost of the intervention will be evaluated based on questionnaires and data from the planning tool completed by the workers.

**Discussion:**

This study will evaluate the effectiveness and implementation of a 12 - weeks Goldilocks Work intervention with the aim of improving musculoskeletal health among industrial workers. The cluster randomized controlled study design and the evaluation of the implementation, results and costs of the intervention will make it capable of contributing with valuable evidence of how productive work may be designed to promote industrial workers’ health.

**Trial registration:**

Clinical trial registration was assigned 10–09-2021 (ISRCTN80969503). https://doi.org/10.1186/ISRCTN80969503

**Supplementary Information:**

The online version contains supplementary material available at 10.1186/s12889-022-12643-w.

## Introduction

### Background and rationale

Industrial workers have an increased risk for poor musculoskeletal health [1] and shortened working life expectancy [2]. This has been explained by their high physical work demands, shown to be associated with increased risk of musculoskeletal pain [1, 3] sickness absence due to pain [4, 5], and early drop-out from work [2]. Accordingly, a common approach to prevent musculoskeletal pain and fatigue among industrial workers has been to reduce their physical work demands [6, 7]. Despite these efforts, the 2018 round of the Danish Work Environment and Health Study showed that most industrial workers experience pain several days each week, and feel fatigued during work [8]. Pain and fatigue have been associated with reduced work ability [5, 9] and increased sickness absence [5, 10, 11], representing a large economic burden for organizations and society [12]. Furthermore, the current demographic projections of an aging European workforce is likely to increase the burden [13, 14]. Therefore, health promoting initiatives targeting workers with physically demanding jobs are highly warranted.

The Goldilocks Work Principle proposes that occupational physical activity can be designed to comprise a ‘just-right’ balance of physical behaviors, including intense periods, alternating with recovery, that can promote workers’ health and fitness [15]. In prior research we found that industrial workers stand for a large portion of the workday, have little variation in their physical behaviors, limited time for recovery, and limited time at an intensity which would promote cardiovascular fitness[16]. Accordingly, increasing their time spent sitting (to support recovery), their time being active, and their frequency of alternations between these behaviors could promote their musculoskeletal health [7, 15, 17]. If some of the active work time could be performed at a high intensity it might additionally benefit workers’ cardiorespiratory fitness [6].

We previously tested the feasibility of redesigning and implementing work tasks based on the Goldilocks Work Principle among a group of industrial workers in Denmark [16]. Through a participatory process, workers redesigned their work tasks with the intention of moving towards a ‘just right’ physical behavior. We set a pragmatic goal for this redesign to be, 1) an even balance of physical behaviors (i.e., equal amounts of time spent sitting, standing or active), 2) alternations between sitting, standing and active work tasks taking place about once every hour, and 3) performing high intensity work tasks for at least ten minutes every workday [16]. We showed that this intervention resulted in modest changes in physical behaviors towards the intended ‘just right’ goals. Intriguingly, workers reported lower levels of pain and fatigue after a ‘just right’ workday than after a usual workday. In order to investigate the effectiveness of ‘just right’ physical behavior to promote musculoskeletal health among industrial workers, interventions need to be tested on a larger sample using a controlled trial design whilst also monitoring the fidelity of the intervention program and the behavioral changes it introduces.

This protocol describes a cluster randomized controlled trial with the primary objective to evaluate the effectiveness of promoting musculoskeletal health by implementing changes that will move workers towards ‘just right’ physical behavior according to the Goldilocks Work Principle. A secondary objective is to determine intervention effects on behaviors measured using wearable sensors, in terms of ‘just right’ proportions and frequency of alternations between sitting, standing and active behavior during work. Finally, a third objective is to evaluate the implementation of the intervention program, including quality of the program delivery, adherence to the protocol, costs, and the extent to which the intervention was realized.

### Trial design

The Goldilocks Work intervention will use two parallel groups, with an allocation ratio of 1:1. Work teams consisting of 1–7 workers, as already organized at the workplace, will be randomly allocated to either an ‘intervention group’ receiving the intervention, or a ‘control group’ performing work as usual.

## Methods: participants, intervention and outcomes

### Study setting

A large industrial organization in Denmark was recruited for this study. Contacts and enrolment of the workplace was accomplished in collaboration with an advisory group comprising professionals from employer and employee organizations. The organization was selected because it has a large number of employees (> 200), has several production sites where workers primarily performs manual work tasks, and is motivated to participate in the project. At present (i.e., at submission), we have developed the Goldilocks Work intervention, and are conducting the implementation in the organization.

### Eligibility criteria

Inclusion criteria for participants in the recruited organization is employment for ≥ 20 h weekly. Exclusion criteria are; 1) only working night shifts, 2) known at baseline to not be employed during the entire intervention period, and 3) pregnancy.

### Development of the goldilocks work intervention

The intervention was developed in accordance with the four-step procedure recommended for the Goldilocks Work Principle (Fig. 1) [7]. We involved stakeholders from the participating organization as well as a reference group consisting of professionals within industry to participate in the development, as recommended by Wells et al. [18].

**Fig. 1 Fig1:**

The four procedural steps recommended for developing Goldilocks Work interventions, adapted from Holtermann et al. [7]

#### Step 1 and 2

To address steps 1 and 2, we used information from the feasibility study [16] and the Danish PHysical ACTivity cohort with Objective measurements (DPhacto), containing measurements of physical behaviors [19]. Based on this information, we found that work among industrial workers typically consists of a large proportion of standing work, few alternations between sitting, standing and active work tasks, and limited time with high intensity [16, 19]. Furthermore, these workers typically exhibit a low fitness level, a high BMI (> 25 kg/cm^2^), and report pain in neck, shoulder, and lower back [19]. Based on our dialogue with stakeholders at the workplace, we found that among the workers in the present study, musculoskeletal health was the main concern. Specifically, neck, shoulder, and low back pain were identified as an issue for many workers at the participating organization.

#### Step 3

To address step 3, we established three goals to reach; 1) a ‘just right’ composition of physical behaviors (i.e., sitting, standing and active behavior) during work; 2) a ‘just right’ frequency of alternations between work tasks performed sitting, standing or active, and; 3) a ‘just right’ occurrence of periods with high intensity. Based on a collaborative process with the workplace, consisting of talks and discussions with workers, management, work environment representatives, staff representatives and health and safety representatives and with consideration to the context at this specific workplace, we formulated the following explicit ‘just right’ goals:

*The ‘just right’ composition of physical behaviors:* To get a specific estimate of the ‘just right’ composition of sitting, standing and active work we analysed data among industrial workers in the DPhacto cohort [19] to identify the composition associated with the best self-rated overall health, defined as the average composition of the 5% most ‘healthy’ workers [20]. This composition consisted in 65% sitting, 28% standing, 7% active, and was selected to represent ‘just right’ in the planned intervention. The composition is close to the recommendations of 60% sitting, 30% standing and 10% active by the European Agency for Safety and Health at Work [21], and for communicative purposes at the workplace, we used this composition of 60%/30%/10%. Everyone in the collaborative process agreed that this composition was a feasible and relevant goal to aim for.

*The ‘just right’ alternations between sitting, standing and active work tasks:* To determine the ‘just right’ frequency of alternations, we discussed the feasibility of alternating between work tasks during productive work with workers and management at the workplace. The current evidence supporting physical variation to have a protective effect against development of musculoskeletal disorders in working life is not conclusive [22–24]. In our previous study, we observed that workers alternated once during usual work and three times during modified work between sitting, standing and active work tasks. This increase in alternations may have contributed to the observed reduction in pain and fatigue following modified work [16]. Discussions with workers and management at the current workplace revealed limitations in the options for alternating between tasks. At first, we suggested that workers should change task every 30 min, with the intention of limiting pain following prolonged periods of standing [25, 26]. However, management expressed concerns about negative effects on productivity, i.e., that passing on work tasks from one worker to another would occupy a substantial part of the work time. Further, when facing a change every 30 min, workers expressed concerns about never experiencing the satisfaction of completing a work task. Eventually, these discussions resulted in an agreement that changing work tasks every 60 min would be feasible without compromising productivity or affecting workers’ perceptions, while still being a relevant goal to aim for.

*The ‘just right’ periods with high intensity:* Even small amounts of high intensity physical activity can have beneficial health effects [27]. However, explicitly aiming for more time at a high intensity physical activity among industrial workers may neither be feasible nor beneficial, if it, for example, occurs without sufficient time for recovery. When discussing opportunities to perform high intensity physical activity as a part of productive work with the participating workplace, we identified several challenges. The most important challenges were, 1) concern by management and health & safety representative about an increased risk of accidents during production as a consequence of performing work with high intensity; 2) struggles by workers and work environment representatives to find a way to safely introduce periods with high intensity in their current work tasks; 3) concern by the staff representatives about resistance from workers to work with high intensity, since some workers might perceive that as an attempt by management to increase their productivity; 4) concern by the health & safety representative and management that implementing high intensity work tasks would counteract their current safety focus to stay safe by ‘never rushing’. During our discussions, we made extensive efforts to accommodate all these challenges in the intervention. Despite our efforts, we were unable to come up with satisfying solutions, and did not reach any agreement of a feasible and potential beneficial goal to aim for. Consequently, we decided to omit the goal of including periods with high intensity in the ‘just right’ work design from the current intervention.

#### Step 4

We designed a general planning tool (i.e., a modification that could likely be implemented, step 4 in Fig. 1) in Excel (Microsoft Office Professional Plus 2016) with the purpose of providing workers with a specific instrument by which they could organize their work tasks. The purpose of this tool is to have workers modify their jobs towards the ‘just right’ physical behavior. To make the tool implementable and applicable for workers, it will be tailored to their work context. Prior to the intervention, a member from our research team will involve the work environment representatives to identify all relevant work tasks, and then have them determine the typical physical behavior for each task as either sitting, standing or active. To ensure that the tool properly reflects the work context at any time, work tasks can be added or modified (e.g. by changing their predefined physical behavior) during the intervention, based on feedback from workers and the local workplace group. At any time, the planning tool includes the existing work tasks, so that workers can select them from a drop-down list, and plan their working day. In the present study, the planning tool partitions the workday into six blocks of approximately one hour each. The objective for each work team of 1 to 7 workers is to rearrange and swap work tasks in production on a given day until everyone has the best possible ‘Goldilocks index’. The ‘Goldilocks index’ will be generated by the general tool, ranging between 0 and 100 (where 100 is the best score possible) and based on how close the plan is to being ‘just right’. To guide the workers, the ‘Goldilocks index’ is color-coded: red if the index is < 50 points, yellow if the index is 50–79, or green if the index is ≥ 80.

We summarized the decisions made in the 4-step process in a program logic (Fig. 2). The program logic is a visual representation of the intended changes in the intervention program and activities, how they are expected to change physical work behavior, and how that will, eventually, improve the health-related goal [28]. The program logic was used as a simple illustration to share with stakeholders [28] and to guide the planning of the intervention, deciding when to do what, and with whom (Fig. 3).

**Fig. 2 Fig2:**
[figure not shown]
Illustration of the program logic for the intervention developed in collaboration with stakeholders from the participating organization as a result of the 4-step model of the Goldilocks Work Principle.

**Fig. 3 Fig3:**
[figure not shown]
Timeline of the 12-week intervention period.

### Implementation plan for the goldilocks work intervention

Because the intervention is conducted at the workplace, fidelity towards the implementation of the intervention program is crucial when assessing its effectiveness [29]. Fidelity is defined as the degree to which an intervention is implemented as prescribed in the original protocol, or as intended by the program developers [30]. Thus, the intervention program must be implemented with fidelity in order for the desired behavior changes to happen and eventually result in the expected health outcome, as visualized in the program logic (Fig. 2) [31].

We selected four strategies to successfully implement the intervention program (Table 1). The main considerations when selecting these strategies were the required time resources, the feasibility of conducting the strategies, and previous experience from within the local workplace group regarding implementation of new initiatives in the organization. Additionally, as a part of the development of the planning tool, we defined four key variables that were monitored by the planning tool and fed back to the workers during the intervention (Table 1, audit and feedback strategy). These variables were chosen based on the assumption that they would reveal relevant information about fidelity, such as adherence and actual use of the planning tool [30, 31]. The four variables are; 1) the extent to which workers make work plans using the planning tool; 2) the amount of time workers use to fill out the planning tool; 3) the amount of red, yellow and green workdays that workers plan, and; 4) the extent to which workers can adhere to their plan.

**Table 1 Tab1:** Implementation plan (cf. Proctor et al., [32])

Name of strategy	Definition of strategy	The actors	The action	The target	Temporality	Dose	Implemen-tation outcome affected
Inform about project	Inform about the project aim and requirements for participation	Researchers and team leaders	Present project at weekly status meetings and distribute folders on project and data security	Disseminate knowledge and address questions about wearing sensors and data protection	Before intervention	Three 20 min meetings	Fidelity and participation rate
Conduct educational meeting [33]	Engage stakeholders in disseminating knowledge about planning tool to workers in production	Researchers and local workplace group	Train work environment representatives to use planning tool and select which workers they are responsible for training	Involve and motivate staff to take ownership of the implementation of the intervention	During intervention	One 1.5 h meeting	Fidelity
Audit and feedback [34]	Motivate workers to change organization of their work tasks	Researchers and workers	Provide weekly feedback on four key variables related to the planning tool	Motivate workers to change their physical behavior	During intervention	Weekly e-mails	Fidelity
Organize implementation team meetings [33]	Discuss implementation effort, share lessons learned, and support one another in the group	Researcher and local workplace group	Discuss how intervention should move forward and which initiatives should be prioritized	Involve management and employees to take ownership of the implementation of the intervention	During intervention	Two 1.5 h meetings	Fidelity

Prior to the intervention, we will form a local workplace group at each production site consisting of work environment representatives, and representatives from management, staff and the health & safety department. In organizing this group we will involve stakeholders with the intention of making the process participatory [18], and support implementation fidelity. During the intervention, we will schedule one educational meeting and two implementation meetings inviting the local workplace group to participate (Fig. 3).

The first meeting (i.e., ‘train local workplace group’, Fig. 3) consists of a researcher training/educating the local workplace group to use the tool for planning work tasks. The local workplace group and the researchers then arrange how, when and who should train the workers to use the tool.

The second and third meeting (i.e., ‘meeting with local workplace group’ 1 & 2, Fig. 3) focus on the use of the tool for work planning. During these meetings, researchers will feed information about the implementation and the fidelity back to the local workplace group [29]. Researchers will present and discuss the four key variables in the planning tool as well as inputs from the workers (verbally or via e-mail). Based on this information, the local workplace group will determine relevant initiatives to support implementation of the intervention. (Table 1, organize implementation team meetings).

### Outcomes

#### Primary outcome measure

The primary outcome measure for the trial will be the difference between intervention and control groups in the change of low back pain intensity from baseline to follow up (12 weeks). We chose low back pain as an overall representation for musculoskeletal health (Fig. 2.), since it has a pronounced influence on both work ability [9], sick leave [10], and since it occurs in many pain patterns [35]. Pain intensity will be measured repeatedly on a numeric scale (NRS, 0–10). A question will be sent to the participants in a text message at the end of the workday for five consecutive workdays at baseline (week 1) and five consecutive workdays at follow up (week 12), asking them to rate their low back pain intensity.

#### Secondary outcome measures

Secondary outcomes include:Difference between intervention and control group in the change in physical behavior composition (i.e., sitting, standing and active), measured using accelerometry for five workdays at baseline and five workdays at follow up.Difference between intervention and control group in the change in accumulated time in bouts of sitting, standing and active, measured using accelerometry for five workdays at baseline and five workdays at follow up. Bout length will be defined as either short (< 5 min), medium (5-30 min), or long (> 30 min).Differences between intervention and control group in the change in perceived fatigue and energy level, perceived physical exertion, and self-rated productivity measured using a numeric scale from 0–10 for five workdays at baseline and five workdays at follow up.Adherence to the intervention program measured through participation rates at planned meetings, and records of planned *and* conducted activities during the intervention.Use of the planning tool measured through the number of completed planning tool schedules.Quality of the program delivery measured using questionnaires following training and implementation meetings with the local workplace group.Cost-effectiveness of the intervention, i.e. the ratio of incremental cost and incremental change in low back pain intensity.

### Participant timeline

The schedule of enrolment, intervention and assessment is presented in Table 2. Together with the organization, we found suitable and interested production sites. Within these participating production sites we will randomize clusters (i.e., teams of workers), to either intervention or control. Subsequently, workers within each cluster will be invited to participate, assessed for eligibility, and followed during the intervention period. Non-participants, loss to follow up, the extent of lost data and the amount of data used for final analysis will be reported.

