## Methods: assignment of interventions

First, workers will be asked by a researcher if they wish to participate in the study. Workers agreeing will then sign an informed consent, and workers declining will be counted as non-participants. After signing the informed consent, workers will complete a physical assessment and following that, they will be verbally informed about their group allocation. This is necessary because we need to plan training activities with the work teams and the local workplace group. Additionally, we need to prepare the planning tool to comply with the specific work tasks of the work teams allocated to the intervention.

Due to the nature of the intervention, it is not possible to blind the workers to their allocation. Additionally, during enrolment, blinding of the assessors is not possible. However, the main outcome, musculoskeletal health, is measured through questionnaires sent out via text messages, and thus, is not affected by our inability to blind the assessors during enrolment. Furthermore, all secondary outcomes are collected with either wearable sensors or questionnaires, and will not be biased by lack of assessor blinding.

Clusters (i.e. teams) will be randomly allocated to the intervention and control groups in a 1:1 ratio. The teams will be allocated using SAS version 9.4 and the function RANUNI, which returns a number generated from a uniform distribution on the interval (0, 1) [39]. The randomization process will be performed separately for each production site, i.e., the randomization will be stratified. Clusters within a production site receiving values in the lower half of numbers drawn at that site will be assigned to the intervention, and clusters with values in the upper half will be controls. A data manager not otherwise involved in conducting the intervention will generate the allocation sequence for each production site.

Intervention and control workers will be present at all included production sites. This allocation procedure was chosen to reduce the risk of bias due to changes in contextual factors (e.g., change in management, structural changes, or supply chain challenges) during the intervention period, which have been shown to occur quite often [40]. Furthermore, it may also reduce potential bias from contextual differences that may exist between sites, such as differences in work tasks, restrictions in production complicating work planning, or how machines are operated.

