### Strengths and limitations

The 4-step procedure and participatory approach that guided the development of the program logic and the intervention is a strength of this protocol. The cluster randomized controlled design with randomization performed at each production site is a strength because it reduces potential bias. The planning tool adapted to the workers’ context is a strength because it offers an easy-to-use and practical approach for their own planning of work tasks to change behavior. The approach of feeding back information from the planning tool to the workers is also a strength that can improve the likelihood that workers’ behavior is changed [34]. Furthermore, the information collected about the implementation process is a strength because it may inform details about who did what when, and explain why things turned out as they did.

A limitation is that participants are not blinded to their allocation; this can increase the risk of selection bias. However, workers will not receive knowledge of their allocation until after they completed their eligibility screen and health check. Another limitation is the short duration of the study (i.e., 12 weeks), since it may take longer to effectively implement changes in physical behavior and thus effectively improve musculoskeletal health. However, even if the intervention is not effective, the workers and the workplace will gain valuable knowledge about their work context, the current physical behavior, and which changes that may improve workers’ health on the long term.

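### Teams are randomised before workers are invited and screened, and nothing says the allocation is concealed from those who recruit, so recruitment could depend on the arm

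*Protocol article*

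**What the plan says.** *Participant timeline* sets the order. First, "Within these participating production sites we will randomize clusters (i.e., teams of workers), to either intervention or control". Then, "Subsequently, workers within each cluster will be invited to participate, assessed for eligibility, and followed during the intervention period". The same section promises to report non-participants and losses, but does not say by arm.

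*Methods: assignment of interventions* describes enrolment from the worker's side. It opens with "First, workers will be asked by a researcher if they wish to participate in the study" and continues: "After signing the informed consent, workers will complete a physical assessment and following that, they will be verbally informed about their group allocation". The reason given for telling workers then is the need to plan training and to prepare the planning tool for the intervention teams. On blinding it states: "Additionally, during enrolment, blinding of the assessors is not possible". It regards this as harmless because pain is reported by text message and the secondary outcomes come from sensors or questionnaires. A data manager not otherwise involved in conducting the intervention generates the sequence for each site. The section does not say when the sequence is drawn relative to consent, or who sees it once drawn.

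*Strengths and limitations* acknowledges the issue in part: "A limitation is that participants are not blinded to their allocation; this can increase the risk of selection bias". It offers one safeguard: "However, workers will not receive knowledge of their allocation until after they completed their eligibility screen and health check".

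**The concern.** In a cluster trial the draw balances teams. Workers within teams are comparable between arms only if entry to the trial does not depend on the arm. When individuals are invited after their team has been allocated, who is approached, how persistently, and who agrees can all differ by arm. Intention-to-treat keeps recruited workers in the arm of their team, but it cannot bring back those who were not recruited.

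The article answers two neighbouring questions and leaves this one open. Its defence of unblinded assessors concerns how outcomes are measured, not who is recruited. Its acknowledgement of selection bias concerns what participants know, not what recruiters know.

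The trial is small: 28 teams are expected, about 14 per arm, and about 22 of 110 eligible workers are expected not to take part. A handful of arm-dependent refusals could alter the baseline mix.

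**Working it through.** **Order of events.** *Participant timeline* is explicit: draw, then invitation, then eligibility. *Methods: assignment of interventions* starts with the invitation and describes the random allocation later, without dating the draw. The two accounts can be read together (draw first, disclosure to workers later), but the text does not settle it. The timeline figure and the enrolment schedule are not shown in the copy reviewed.

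**Who could know the arm during recruitment.**
- *Workers approached first*: not told until after consent, screening and the physical assessment.
- *Recruiting researchers*: not stated. That assessors cannot be blinded at enrolment makes most sense if the allocation already exists and is known to them, but this is inference.
- *Team leaders*: not stated. The implementation plan (Table 1) has them presenting the project together with the researchers before the intervention.
- *Teammates not yet approached*: allocation is by team and disclosure is verbal. Nothing says that disclosure waits until the whole team or site has been enrolled.

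**Participant flow (*Sample size*).** 110 × 0.80 = 88 participants; 88 × 0.80 = 70.4, stated as 70. This reproduces. Non-participants: 110 − 88 = 22, or about 11 per arm.

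**Illustrative size.** The article gives no figure for this bias, so the inputs D and r below are assumptions.
- p = 0.80, participation (*Sample size*).
- D = 1 to 3 points, the baseline pain difference between participants and non-participants produced by selection (assumed).
- r = 0.5 to 0.7, the correlation between baseline and follow-up pain, with equal variances (assumed).

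The eligible mean is p × (participant mean) + (1 − p) × (non-participant mean). Participants in an arm with selection therefore differ from all eligible workers by (1 − p) × D. If selection acts in one arm only:
- Baseline imbalance = 0.20 × D = 0.2 to 0.6 points.
- A fraction r of this persists at follow-up, so bias in the change score = (1 − r) × 0.20 × D.
- Smallest: (1 − 0.7) × 0.20 × 1 = 0.06. Largest: (1 − 0.5) × 0.20 × 3 = 0.30.

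If selection acts in opposite directions in the two arms, these double to 0.12 to 0.60 points.

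**Effect on the test.** If the article's detectable difference of 1.5 points (two-sided 5%, 80% power) is taken at face value, the implied standard error is 1.5 / 2.80 = 0.535. Type I error then rises from 5% to 5.1%–8.7% with one-arm selection, and to 5.6%–20% with opposite selection.

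These rates depend on that standard error. With 35 per arm, the stated variance of 9.3 and r = 0.5, the change score has variance 2 × 9.3 × (1 − 0.5) = 9.3 and standard error √(2 × 9.3 / 35) = 0.729, ignoring clustering. The upper ends fall to about 7.0% and 13%. On these inputs the 1.5 points does not reproduce either (2.80 × 0.729 = 2.04); that is a separate matter and does not bear on this point.

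**The case against.** The strongest reply is that, by plan, workers decide without knowing their arm. Disclosure follows consent, screening and the health check, and the article says so twice. This stands, and it removes the most direct form of self-selection for anyone who has not heard from a colleague.

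The eligibility criteria also leave little room for discretion: weekly hours, night shifts only, known end of employment and pregnancy are largely matters of fact. The teams already exist and the pool is finite. Selective screening is therefore a minor risk; the exposure lies in who is approached and who consents.

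An independent data manager generates the sequence, and a reader might infer from this that it is concealed. The text supports independent generation only and is silent on concealment. Equally, a reader might infer that recruiters are stated to know the allocation. They are not: the sentence on blinding concerns assessors during enrolment and does not say who holds the sequence.

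A larger bias can be constructed. Refusal of 10% in one arm and 30% in the other, with a 2-point difference in pain change between refusers and participants, gives 0.20 × 2 = 0.4 points. That requires refusal to differ widely by arm although workers are not told their arm, and a difference in change larger than the 1.5-point target. The documents support neither input.

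Finally, early allocation has a stated practical purpose, and *Study setting* says implementation was already under way at submission. Re-ordering may no longer be possible at every site.

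**Conclusion.** The point holds as a weakness of the stated sequence. Recruitment follows the draw, no text conceals the draw from recruiters or team leaders, and the article's safeguard and defence do not reach those routes. That recruiters know the allocation is a fair inference, not a stated fact, and the two accounts of the order need reconciling.

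A reader might conclude that comparability between arms is lost. The documents do not support that: they show an open route, not that selection occurred. The size is unknown. Under the assumptions above, bias is 0.06 to 0.30 points with selection in one arm, and reaches 0.60 only at the extreme of opposite selection, against a target of 1.5 points. This warrants correction because the remedy mainly re-orders steps already planned.

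**What to change.** Reconcile *Participant timeline* with *Methods: assignment of interventions* so that one order is stated.

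1. **Sites not yet randomised.** Invite, consent and screen all workers on the team rosters, preferably completing the baseline pain week as well, before the data manager draws the sequence. Finishing baseline pain first also keeps that half of the change score from being rated by workers who know their arm.
2. **If the draw must come earlier** to prepare training and tools, the data manager withholds it from recruiters, team leaders and workers until enrolment at that site closes. Individual verbal disclosure after each physical assessment would then be replaced by release once per site.
3. **Sites already randomised.** Report eligible, invited, declined and excluded workers, and baseline pain, by arm. This makes differential recruitment visible but does not undo it.

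The cost is lead time. Baseline is in week 1 and tool use starts in week 3, so a draw after the baseline week leaves about one week for team-specific training and tool tailoring. Whether that is enough cannot be judged without the timeline figure; option 2 is there if it is not. No sample-size figure changes.
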